### Selection of subjects

Eight health centres in the Albacete, Zaragoza and Vigo Health Areas have been chosen for strategic reasons. To prevent contamination bias, the control group participants will belong to areas different to those of the experimental groups. Accordingly, participants will be randomised on a health-area basis, with subjects then being consecutively selected.

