### Study location and subjects

Participants will be recruited from among patients attending family medicine outpatient facilities at 8 health centres situated in three health areas of three of Spain’s Autonomous Regions (Comunidades Autónomas), namely, Castile-La Mancha (Albacete Health Area), Aragon (Zaragoza Health Area) and Galicia (Vigo Health Area). The target population is made up of all persons aged 18 years or over with diagnosis of hypercholesterolaemia, with the population eligible for study comprising hypercholesterolaemic subjects of this age drawn from the eight health centres in the above three participating health areas.

The study inclusion criteria require that candidates: a) be diagnosed with hypercholesterolaemia, as defined according to the criteria stipulated in the cardiovascular prevention guidelines of the 2009 Prevention Activities and Promotion of Health Programme (total cholesterol of 250 mg/dl or higher); and, b) be patients aged 18 years or over attending any of the participating health centres. The following individuals will be excluded: a) any person hindered from participating in the follow-up of the proposed intervention, e.g., illiterate subjects and non-users of mobile telephones; b) any person with a physical disability or impairment which prevents him/her from attending the follow-up visits; and, c) any person suffering from a significant chronic organic or psychiatric disease.

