### Subject follow-up

Subjects will be monitored for a period of two years.

Selection will be made at primary care outpatient facilities, inviting patients who meet the inclusion criteria to participate in the study. Once they have given their consent, such patients will then be given an appointment for an initial visit and analysis.

During the initial visit, patients will be randomised to one of the two groups. Data will be collected from all participants covering medical history (socio-demographic variables, personal and family background, lifestyle habits), physical examination (anthropometric parameters, blood pressure), analysis (lipid profile, glucose) and calculation of cardiovascular risk. The routine standard recommendations, pharmacological and non-pharmacological, will be made for their treatment. An appointment will be made for the next visit.

Participants included in the intervention group will be given printed matter describing the disease and its management, along with treatment-compliance check cards, and they will be informed about the frequency and content of the mobile-telephone text messages that they will receive. Disease-management reminders will be dispatched every 15 days and reminders about attendance at pending appointments or missed appointments will be sent according to the follow-up dates.

With respect to follow-up, after the initial visit, 5 more will be made: these will take place at 2, 6, 12, 18, and 24 months. At each of these visits, anthropometric parameters (weight, BMI and waist circumference), blood pressure figures, lipid profile (total cholesterol, LDL-C, HDL-C and triglycerides), glucose and clinical history data will be recorded, and cardiovascular risk will be calculated. Data evaluating compliance with or adherence to treatment guidelines will be obtained for both groups of patients. Data on satisfaction will solely be recorded during the final visit, and then only for subjects in the intervention group.

Any of the following circumstances will be grounds for termination of the study in the case of any given participant: completion of the observation period (2 years); violation of the protocol; intercurrent disease that renders continuation of the intervention impossible; and withdrawal from the study/withdrawal of consent.

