## Discussion

Finding a type of action that could yield a higher success rate in the compliance and control of subjects with hypercholesterolaemia is fundamental when it comes to optimising available resources and improving the prevention and treatment of cardiovascular disease. This is why we feel that the most effective strategy will have to include activities targeted at enhancing knowledge about dyslipidaemia, reminding patients about guidelines and facilitating a higher patient participation rate. Similarly, we propose an action that is targeted, not only at pharmacological adherence, but also at the remaining recommendations for improving control of hypercholesterolaemia.

The results of the study will provide extremely useful information about the effectiveness of the proposed strategy of improving compliance in the prevention and management of cardiovascular disease based on increased control of lipid profile plasma levels. Should this intervention prove effective, a recommendation could then be issued on the application of the combined strategy to subjects with hypercholesterolaemia. Since it is a simple and relatively inexpensive intervention, it could be included as a recommendation in the respective clinical practice guidelines.

Selection biases will be reduced by using a randomisation procedure because it is not the researcher who allocates the intervention, and so any factor that might influence participation would affect both groups to the same degree. Likewise, confounding bias will be reduced by the effect of random chance, as a result of which any determinants that might influence the final result will tend to be shared between the intervention and control groups.

There is the possibility that the sample may not be representative of all eligible subjects, owing to differences between the persons who agree and those who do not agree to participate, posing a problem of external validity if the non-response rate proves to be high. For instance, persons who agree to participate in the study may possibly be more predisposed to follow guidelines than are the remaining candidates.

There could be a bias in data-collection due to the effect of regression towards the mean, applicable to analytical results. There is also the possibility of a risk of differential losses in follow-up between the groups compared, due to the duration of the study.

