With the help of the health professionals who usually attend to the patients, every effort will be made to the reduce the number of losses to follow-up. Even so, in a case where such losses proved to be high and were not caused at random, a bias could appear in the measurements and compromise the study’s validity, due to the low representativeness of the sample.

The intervention proposal (combined strategy of improving adherence) does not allow for application of masking techniques, with only blind evaluation of results being feasible.

In view of the fact that the study is to be undertaken at various health centres in different Autonomous Regions, possible sources of error and their respective control mechanisms might be: protocol deviations (appropriate staff training will be undertaken); and data errors or omissions (these will be minimised using techniques for identifying anomalous data, and regular reports).

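### The protocol contradicts itself on the unit and timing of randomisation; if the area-based version is followed with the three named areas as units, arm cannot be separated from region

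*Protocol article*

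**What the plan says.** Study location and subjects places the trial in "8 health centres situated in three health areas of three of Spain’s Autonomous Regions", one area per region.

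Two sections then describe how patients reach an arm:

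- Selection of subjects, to prevent contamination: "the control group participants will belong to areas different to those of the experimental groups". It adds that "participants will be randomised on a health-area basis, with subjects then being consecutively selected".
- Subject follow-up: eligible patients are invited. "Once they have given their consent, such patients will then be given an appointment for an initial visit and analysis". Then "During the initial visit, patients will be randomised to one of the two groups".

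The Abstract and Design call the trial randomised and parallel-group without naming a unit. Sample size uses a comparison of two independent proportions, and Statistical analysis compares proportions with a chi-squared test. Neither mentions clusters. The Discussion relies on randomisation to deal with selection, stating that "any factor that might influence participation would affect both groups to the same degree", and says that chance will reduce confounding. It also says that the intervention "does not allow for application of masking techniques, with only blind evaluation of results being feasible".

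**The concern.** The two accounts differ in both unit and order. In one, an area receives its arm and patients are enrolled afterwards. In the other, a patient consents and is then allocated. If patients are randomised at a visit in their own centre, the arms cannot lie in different areas. If areas are allocated, nothing is left to randomise at the visit. A fuller protocol could not make both true, so this is not a matter of an article leaving out detail.

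The choice decides what the trial can show. Under patient randomisation the planned comparison estimates the effect of the intervention. Under allocation of three areas it compares regions that also differ in intervention, and the protection that the Discussion claims from randomisation is largely lost. The authors intend a practice recommendation if the strategy proves effective, so the difference matters.

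**Working it through.** **1. The plan's own figure.** Inputs from Sample size: 55% v 75%, two-sided α 5%, power 90%. Per-group n = [1.960·√(2·0.65·0.35) + 1.282·√(0.55·0.45 + 0.75·0.25)]² / 0.20² = 117.4, so 118 (128 with continuity correction). The stated 155 does not reproduce at 90% power; it corresponds to 95% power with continuity correction. That is a separate matter. What counts here is that the formula assumes independently allocated patients and that the excess over 118 is not presented as an allowance for clustering.

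**2. Arms and areas.** Three areas in two arms can only split 1 v 2. With area effects a₁, a₂, a₃ on the lipid-control rate and true effect δ, the expected difference when area 1 is one arm is, up to sign, δ + a₁ − (weighted mean of a₂ and a₃). The area contrast has coefficient 1. The logistic regression in Statistical analysis cannot estimate it apart from δ, because that contrast coincides with the arm indicator. More patients reduce sampling error only.

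**3. Size of a regional difference.** The documents give no figure, so this is an assumption: 5 points is 5/20 = one quarter of the planned effect, and 10 points is 10/20 = one half.

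**4. Randomisation test on the areas.** There are 3 ways to choose the single-area arm, or 6 if its label is also random. Swapping labels leaves the absolute difference unchanged, so the smallest two-sided p is 1/3 (or 2/6 = 1/3). A model-based t-test on the three areas has 1 degree of freedom and a critical value of 12.7; it is not bound by 1/3, but it is very weak.

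**5. Error rate of the patient-level test.** No intracluster correlation (ICC) is given, so a range is assumed. Take an overall rate of (0.55 + 0.75)/2 = 0.65, 155 per arm, and the two-area arm shared equally between its areas.

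- Naive SE = √(0.65·0.35·2/155) = 5.4 points.
- Area SE = √(ICC·0.65·0.35)·√(1 + 1/2).
- Total SE = √(area SE² + naive SE²·(1 − ICC)).
- True type I error = 2[1 − Φ(1.96 × naive SE / total SE)].

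| Assumed ICC | Area SD (points) | Area SE (points) | Total SE (points) | True type I error at nominal 5% |
|---|---|---|---|---|
| 0.01 | 4.8 | 5.8 | 7.9 | 18% |
| 0.02 | 6.7 | 8.3 | 9.8 | 28% |
| 0.05 | 10.7 | 13.1 | 14.1 | 45% |

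**6. If smaller catchments are the units.** With eight clusters of 310/8 = 38.75 patients, the design effect is 1 + 37.75·ICC: 1.38, 1.75 and 2.89 at ICC 0.01, 0.02 and 0.05. The unadjusted chi-squared test then has a type I error of 9.5%, 14% and 25%. With 155 per group, power that allows for clustering is 89%, 80% and 59%. These powers use normal critical values and are optimistic: with 8 − 2 = 6 degrees of freedom the critical value is 2.45, not 1.96. An assumed 4 v 4 split has 70 allocations, so a two-sided p of 2/70 = 0.029 becomes attainable.

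**7. Order of recruitment.** Under Selection of subjects, the area's arm exists before its patients are selected, and the intervention cannot be masked. Staff and patients may therefore know the arm at invitation. Under Subject follow-up, consent comes first and this does not arise.

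**The case against.** The contradiction itself has no good answer: no other section says which account governs. The objections concern what follows from it, and several stand.

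- **A reader might infer that the trial is confounded with region outright.** The documents do not support that. It follows only if the account in Selection of subjects is the one used; under Subject follow-up neither the confounding nor the early knowledge of the arm arises.
- **Three units is an inference.** That section names the three health areas and then refers more loosely to areas. It could mean smaller areas or centre catchments, and then the single-region arm and the floor of 1/3 would not follow.
- **A reader might infer that recruiters pick patients to suit the arm.** Consecutive selection limits that. What it does not do is conceal the allocation or prevent patients from agreeing at different rates once the arm is known.
- **A randomisation p-value of 1/6 might be quoted.** It is one-sided, and Sample size specifies a two-sided test.
- **A reader might take the Discussion to claim that confounders will be equal in the two groups.** It says only that confounding will be reduced and that determinants will tend to be shared. Its statement about participation factors carries no such hedge.
- **Regional differences are undocumented.** Both arms are to be managed under the same European guidelines, which should narrow differences in care. It does not guarantee equal lipid-control rates across three regions.

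**Conclusion.** The concern holds as a definite contradiction with conditional consequences. The unit and timing of randomisation are stated in two ways that cannot both be true, and this must be resolved before the design can be described or analysed.

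If area allocation applies with three areas, the effect of the intervention is not separable from that of region, at any sample size and with any covariates. The patient-level test would have a type I error of about 18% to 45% for assumed ICCs of 0.01 to 0.05. The Discussion's claim about participation factors would be unsupported, and its hedged claim about confounding would carry little force with three units. With about eight smaller clusters the damage is less, but clustering and unconcealed recruitment remain. If patients are randomised after consent, none of these consequences applies and only the conflicting text needs correction.

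The documents do not show which account was meant to apply, so it would go too far to conclude that the trial is invalid.

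**What to change.** State one unit of randomisation and make the Abstract, Design, Sample size, Selection of subjects, Subject follow-up, Statistical analysis and Discussion agree with it.

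- **If patients are randomised:** delete the sentences on areas in Selection of subjects and stratify by centre. This costs wording and a stratified list, and the risk of contamination has to be accepted or handled in another way.
- **If clusters are needed against contamination and allocation has not been done:** randomise centres within each area, so that every area contributes to both arms. Identify eligible patients before the centre's arm is disclosed. Account for clustering by centre in the analysis, with a method suited to few clusters, and restate the power with an explicit ICC assumption. This assumes at least two centres per area, which is not stated. Eight centres remain few: if the areas held 4, 2 and 2, each split evenly, there would be 6 × 2 × 2 = 24 allocations and a smallest two-sided randomisation p of 2/24 = 0.08. More centres may be needed. The cost is an amendment, a new allocation list and probably a larger trial.
- **If areas are already allocated:** describe the trial as an area-allocated comparison, correct the Discussion's statements on selection and confounding, and limit the conclusion accordingly. The Ethics approval section reports signed consent in the past tense, so this may be the only option left. It costs wording and a weaker claim.

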### Intervention

Participants in the intervention group will be supplied with: a) printed matter containing information on the disease and its management (this will be handed out at each of the follow-up visits); b) mobile-telephone text messages containing guideline summaries, reminders of forthcoming appointments and/or arrangements for making new appointments in the event of non-attendance (in the periods between visits); and, c) self-report cards to check compliance with recommendations (across the entire follow-up).

Both groups, intervention and control, will receive routine recommendations from their GPs, in accordance with current European clinical practice guidelines on the management of hypercholesterolaemia and cardiovascular risk (European Guidelines on Cardiovascular Disease Prevention in Clinical Practice: Fifth Joint Task Force of the European Society of Cardiology and other societies and Guidelines for Management of Dyslipidaemias: the Task Force for the Management of Dyslipidaemias of the European Society of Cardiology and the European Atherosclerosis Society).

### Subject follow-up

Subjects will be monitored for a period of two years.

Selection will be made at primary care outpatient facilities, inviting patients who meet the inclusion criteria to participate in the study. Once they have given their consent, such patients will then be given an appointment for an initial visit and analysis.

During the initial visit, patients will be randomised to one of the two groups. Data will be collected from all participants covering medical history (socio-demographic variables, personal and family background, lifestyle habits), physical examination (anthropometric parameters, blood pressure), analysis (lipid profile, glucose) and calculation of cardiovascular risk. The routine standard recommendations, pharmacological and non-pharmacological, will be made for their treatment. An appointment will be made for the next visit.

Participants included in the intervention group will be given printed matter describing the disease and its management, along with treatment-compliance check cards, and they will be informed about the frequency and content of the mobile-telephone text messages that they will receive. Disease-management reminders will be dispatched every 15 days and reminders about attendance at pending appointments or missed appointments will be sent according to the follow-up dates.

With respect to follow-up, after the initial visit, 5 more will be made: these will take place at 2, 6, 12, 18, and 24 months. At each of these visits, anthropometric parameters (weight, BMI and waist circumference), blood pressure figures, lipid profile (total cholesterol, LDL-C, HDL-C and triglycerides), glucose and clinical history data will be recorded, and cardiovascular risk will be calculated. Data evaluating compliance with or adherence to treatment guidelines will be obtained for both groups of patients. Data on satisfaction will solely be recorded during the final visit, and then only for subjects in the intervention group.

Any of the following circumstances will be grounds for termination of the study in the case of any given participant: completion of the observation period (2 years); violation of the protocol; intercurrent disease that renders continuation of the intervention impossible; and withdrawal from the study/withdrawal of consent.

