### Sample size

The sample size needed for analysis will be calculated using a two-sided test, based a clinically relevant difference of 20% in the proportion of subjects who attain the lipid control targets, i.e., 55% in the control group, according to data furnished by previous studies (Kotseva et al. [8, 11]; Bueno et al. [18]), and 75% in the group undergoing the proposed intervention. Assuming a statistical power of 90% and an α error of 5%, the estimated sample size would then be 155 subjects in each group (total of 310 subjects). Assuming an expected proportion of losses of 15%, the final size of each group would be 179 subjects (an overall total of 358).

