### Statistical analysis

We will compare the variables of interest and the stratification and potentially confounding variables at baseline in both groups. The homogeneity of the two groups will be ascertained in terms of the baseline values of the study variables (Student’s t and chi-squared test, depending on the nature of the variables).

The subjects in the two groups will be classified into different LDL-C and total cholesterol reduction levels, and an initial crude analysis will be performed to assess the following parameters together with their respective 95% confidence intervals (CIs): absolute benefit increase (ABI); relative benefit increase (RBI); and number needed to treat (NNT).

Incidence of the outcome variables will be described and compared (proportion of subjects with appropriate control of lipid parameters and proportion of those who were guideline compliers) in both groups for each follow-up period (tests of comparison of proportions: Chi-squared test). Comparison of variations in lipid profiles in each group across the study will be made using the Student’s T-test or its non-parametric alternative (Mann–Whitney U test); and changes in the parameters in each group will be analysed using the T-test for repeated measures.

The possible existence of confounding factors or interaction of other variables in the relationship between the proposed intervention and the outcome variables will be assessed with the aid of logistic regression models (dependent variables: control of lipid parameters and therapeutic adherence). For continuous variables, assessment will be made using multiple linear regression.

Analysis will be conducted on an intention-to-treat basis, with all randomised patients being included in the analysis of effectiveness in accordance with their randomised group, regardless of the intervention received. In addition, a protocol analysis will also be performed for the main variables.

All analyses will be performed using the SPSS v20.0. computer software programme.

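### Participants leave the study on a protocol violation, and only one arm is reminded of visits, so the promised intention-to-treat analysis is not protected against bias in either direction

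*Protocol article*

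**What the plan says.** Four parts of the protocol article bear on this point.

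- **Subject follow-up** gives the grounds on which an individual participant's study ends. Besides reaching two years and withdrawal, they include "violation of the protocol; intercurrent disease that renders continuation of the intervention impossible". Visits are planned at 2, 6, 12, 18 and 24 months, with a lipid profile at each, in both groups.
- **Statistical analysis** promises intention to treat, with "all randomised patients being included in the analysis of effectiveness in accordance with their randomised group, regardless of the intervention received". A per-protocol analysis of the main variables is planned in addition.
- **Intervention** lists, for the intervention group, text messages that include "reminders of forthcoming appointments and/or arrangements for making new appointments in the event of non-attendance". Subject follow-up repeats this in its paragraph on the intervention group. No such messages are described for controls.
- **Discussion** acknowledges the danger: "There is also the possibility of a risk of differential losses in follow-up between the groups compared". It puts this down to the length of the study. It adds that non-random losses could compromise validity, and promises a general effort, through the usual health professionals, to keep losses low.

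**The concern.** The termination list puts protocol violation and inability to continue the intervention beside completion of the two years. On its natural reading, termination therefore ends observation and not only the intervention. Intention to treat exists to keep in the comparison the patients who deviate, and this rule would remove them before the 24-month outcome is measured. The planned per-protocol analysis already deals with deviations, so ending their follow-up serves no stated purpose.

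The trial tests a strategy to improve adherence. A participant who violates the protocol may plausibly also be less likely to reach the LDL-C target. In addition, one arm is prompted to attend the visits at which the primary outcome is measured, and is rebooked when a visit is missed. The intervention can then change who is measured as well as what is measured. The Discussion does not name this route to differential loss.

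At stake is the primary comparison. If losses differ between arms and are related to outcome, the estimated effect can be pushed down or up, depending on how missing values are treated.

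**Working it through.** **1. The sections side by side.** Subject follow-up: a violation, or disease that prevents the intervention, ends the participant's study, and no later measurement is described. Statistical analysis: all randomised patients are analysed whatever they received. Both can be carried out fully only if LDL-C is still measured after such a termination, and the article does not say that it is.

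**2. The plan's own figures.** The Sample size section allows 15% losses overall, not split by arm, and takes 155 per group to 179. This reproduces as 155 × 1.15 = 178.25, rounded up to 179. With 15% lost, 179 × 0.85 ≈ 152 remain. At the design rates ("55% in the control group, according to data furnished by previous studies" and "75% in the group undergoing the proposed intervention", two-sided 5%), 152 per group still gives about 96% power, so the issue here is bias and not power. The 155 does not itself follow from the stated inputs at 90% power: the usual formula gives 118, or 128 with continuity correction. That is a separate matter and has no bearing on this point.

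**3. Illustration of size.** From the document: 55% at target, 179 per arm, 15% average loss. Assumed: no true effect, so 55% in both arms; losses L of 10% (intervention) and 20% (control), which average 15%; a proportion q = 30% of the lost at target, the same in both arms.

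*Attenders only*, rate = (0.55 − L·q)/(1 − L):
- Intervention: (0.55 − 0.10 × 0.30)/0.90 = 0.52/0.90 = 57.8%
- Control: (0.55 − 0.20 × 0.30)/0.80 = 0.49/0.80 = 61.3%
- Difference: about −3.5 points

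*Missing counted as failure*, rate = 0.55 − L·q:
- Intervention 52%, control 49%, difference +3.0 points
- SE = √[(0.52 × 0.48 + 0.49 × 0.51)/179] = 0.0528, so the shift is 0.03/0.0528 = 0.57 SE
- Chance of a significant result favouring the intervention: P(Z > 1.96 − 0.57) ≈ 8%, against a nominal 2.5%

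**4. Range over the assumptions** (difference in points, true effect zero):

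| Losses, intervention v control | Lost at target | Attenders only | Missing = failure |
|---|---|---|---|
| 15% v 15% | any equal rate | 0 | 0 |
| 10% v 20% | 55% | 0 | +5.5 |
| 10% v 20% | 30% | −3.5 | +3.0 |
| 10% v 20% | 25% | −4.2 | +2.5 |
| 5% v 25% | 55% | 0 | +11.0 |
| 5% v 25% | 30% | −7.0 | +6.0 |
| 5% v 25% | 25% | −8.4 | +5.0 |

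The design difference is 20 points. The attenders-only bias vanishes when loss is unrelated to outcome (55% of the lost at target). Both biases vanish when losses and the lost patients' target rates are equal between arms.

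**The case against.** The strongest reply is that the document gives no violation rate, no loss by arm and no link between loss and outcome, so nothing shows that the result will be biased. That stands. A reader might infer that an unbiased intention-to-treat analysis is impossible; the text does not support this, and several scenarios above give no bias.

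A reader might also infer that inability to continue the intervention can arise in one arm only. That is not established. The article also uses the word intervention for what happens at the GP's practice, and the list applies to any participant. Nor is a protocol violation defined as non-adherence. Adherence is itself measured in both groups, so ordinary non-adherers are evidently meant to be observed. The link between violation and outcome is plausible but not stated.

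Larger false-positive rates can be produced: about 18% for losses of 10% v 20%, and about 55% for 5% v 25%. They need missing to count as failure, a rule the protocol does not state, together with 55% of the lost at target. With that same 55%, the attenders-only bias is zero. Such figures should not be combined with an attenders-only figure that assumes 30%. Using 30% throughout gives about 8% and 20.5%.

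How missing data are handled may be set out in an analysis plan that is not shown, so its absence is no finding. Reminders are a declared part of the strategy under test and not an error in themselves. All participants are given a next appointment, the effort to limit losses is not confined to one arm, and the article openly discloses the risk of differential loss.

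None of this removes the conflict between the two sections. An analysis plan can choose how to treat missing values, but it cannot supply LDL-C measurements that the follow-up rule stopped.

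**Conclusion.** The concern holds as an unreconciled conflict. As written, participants who violate the protocol or cannot continue the intervention leave observation, while the primary analysis is promised on everyone randomised. That analysis is therefore not protected against bias, in either direction. The one-arm reminders are a further possible source of differential loss, which the Discussion does not identify.

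The size is not known. With no true effect and 30% of the lost at target, losses of 10% v 20% give about −3.5 points among attenders, or +3 points if missing is failure (about 8% favourable false positives). Over the wider range tabulated, the spurious difference runs from about −8 to +11 points, and it is zero under the conditions named above. The loss splits, the target rates among the lost and both ways of treating missing values are assumptions. The false-positive figures also treat patients as independent. The change is worth making because it is cheap and the primary comparison depends on it.

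**What to change.** Reconcile the Subject follow-up and Statistical analysis sections by separating stopping the intervention from leaving the study. State that participants with a protocol violation, or who cannot continue the intervention, keep their scheduled outcome visits, including the month-24 LDL-C, unless they withdraw consent. Deviations are then handled in the per-protocol analysis already planned.

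Report attendance and losses by arm at each visit, and name the one-arm reminders in the Discussion as a possible cause of differential ascertainment.

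Optionally, use one identical recall procedure in both arms for the month-24 blood test. This is a trade-off: it makes outcome measurement more even, but it gives controls a little of what is being tested and so slightly dilutes the reminder contrast.

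The cost is a short amendment, with follow-up at visits already scheduled. The optional recall adds one contact per control participant.
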